## Abstract

**Introduction:**

Weight restoration is a primary goal in anorexia nervosa (AN) treatment. Recent studies suggest that addressing physical activity urges in patients with AN is a promising target to facilitate weight restoration. This trial will evaluate the feasibility of a virtual reality (VR)-based intervention as an add-on treatment to psychotherapy to improve activity urges and, consequently, initial treatment responses on core outcomes as targeted per AN treatment guidelines.

**Methods and analysis:**

This single-centre feasibility trial adopts the single-blind, two-arm design and outcome measures of an intended full-scale randomised controlled trial (RCT) in order to establish that all necessary trial components work together as intended. It will evaluate feasibility as the primary endpoint and compare changes in ratings of the urge to be active between patients with AN randomly assigned to receiving VR intervention sessions and patients with AN in a control procedure. The feasibility of the full-scale RCT will depend on whether patients (1) will evaluate the experience as acceptable, (2) tolerate VR side effects and (3) will adhere to the intended intervention schedule. We define a set of three-tiered, formal progression criteria and employ a ‘traffic light system’ demarcating go (green), amend (amber) and stop (red) signals for advancing to the full-scale RCT.

**Ethics and dissemination:**

The study was approved by the ethics committee of the Ruhr University Bochum’s Medical Faculty at Campus East-Westphalia (AZ 2024-1296, 9 December 2024). Patients have to provide written consent before taking part in the study. The findings will be published with open access.

**Trial registration number:**

DRKS00035681, German Clinical Trials Register.

STRENGTHS AND LIMITATIONS OF THIS STUDYThe feasibility trial adopts the single-blind, two-arm design and outcome measures of the intended full-scale randomised controlled trial.Sample size estimation is based on a formalised set of feasibility criteria.The study is monocentric.Objective physical activity levels are not assessed.

## Introduction

### Background and rationale

 Anorexia nervosa (AN) is a severe mental disorder that typically begins during adolescence and is characterised by significant weight loss or failure to gain weight appropriately for age due to restrictions of energy intake, an intense fear of weight gain and a disturbed body image.^1^ Its subgroups include a restricting type and a binge-eating/purging type, presenting with episodes of eating large amounts of food followed by weight control behaviours such as self-induced vomiting. AN exhibits the highest prevalence and incidence rates among young women and adolescent girls, with lifetime prevalence estimates ranging from 1.7 to 3.6%^2^ and yearly incidence ranging from 120.0 to 318.9 per 100 000 individuals.^3^ In men, prevalence and incidence rates are typically lower by a factor of 10 or more than in women,^4^ although rising steadily over the last three decades.^5^ Highlighting its substantial burden, patients with AN show increased health service utilisation^6^ and an all-cause mortality risk that is 5.9 times higher than in the general population, placing AN among the most lethal mental disorders.^7^ Estimates for Western Europe suggest that, in 2019, premature death and lost quality of life due to AN were responsible for 112.27 disability-adjusted life years per 100 000 individuals.^8^ The treatment and economic costs of AN average €319 million yearly.^9^

#### AN treatment targets

Weight restoration is a primary goal in AN treatment.^10^ Weight restoration is critical for medical stabilisation and sets the stage for long-term recovery.^11^ Studies identified weight gain across inpatient and outpatient settings as a positive predictor of recovery from AN up to 1 year after treatment,^12^,^15^ with early weight gain during the first 3–4 weeks of treatment being a significant predictor of clinical outcomes.^16^,^19^ Next to refeeding and nutritional rehabilitation, psychotherapy for adults and family-based treatments for adolescents are considered first-line treatment options.^20^,^22^ Although treatment often results in temporary weight restoration, patients with AN remain at an exceedingly high risk for relapse, with the majority of studies reporting relapse rates greater than 25% and up to 52% within the first year after successful treatment.^23^ The volatility of treatment responses highlights that addressing maintaining factors of low body weight in AN remains a major challenge^24^ and that novel treatment approaches to augment existing options are urgently needed.^25^

#### Unaddressed maintaining factors of low body weight

Recent studies suggest that addressing physical activity (PA) urges in patients with AN is a promising target to facilitate weight restoration.^26^,^29^ Up to 75% of patients with AN, irrespective of the subtype, show increased PA levels^30^ despite experiencing tiredness and fatigue.^31^,^33^ PA, broadly referring to any body movement produced by skeletal muscle contractions as part of both exercising and non-exercising (eg, standing, walking or fidgeting), substantially increases energy expenditure relative to basal metabolism^34 35^ and contributes to the maintenance of low body weight.^36^,^39^ In a systematic review of the literature, Rizk *et al*^30^ proposed that the urge to engage in PA in patients with AN develops gradually. Initially, individuals engage voluntarily in PA to maximise weight loss at early stages of AN development. However, with increasing AN severity and PA intensity, engaging in PA transitions into a coping strategy to alleviate negative affect and body image concerns, ultimately evolving into an autonomous and compulsive activity drive characterised by diffuse restlessness and aimless, involuntary PA.^33 40^

Increased levels of PA have been linked to the severity of AN psychopathology and associated to longer hospitalisations, poorer treatment outcomes (shorter times to relapse, chronic course of the disorder) and lower life quality.^2931 37 41^,^43^ To facilitate weight gain during nutritional rehabilitation (especially in the initial stages of treatment and for patients with very low weight), abstinence from PA is recommended.^44^ However, patients with AN experience prescribed inactivity as detrimental to their mental well-being and to the management of their condition.^45^ Patients may also still engage in non-exercising PA, such as deliberate (eg, isometric) muscle contractions or more automatic fidgeting, which are difficult to monitor and can negatively impact weight restoration.^46^ Thus, there is a continuing and unmet need to address the urge to be physically active during AN treatment.

#### The potential of virtual reality (VR)-based interventions

In the absence of interventions targeting activity urges, we developed and piloted a concept for a novel VR-based intervention.^28^ Based on the efficacy of VR body exposure techniques,^47^,^53^ we hypothesised that simulated movement within a highly immersive 360° VR environment would support the illusion of actual body movements and effectively alleviate patients’ urge to engage in PA. In a single-arm, proof-of-concept study,^28^ 20 patients with AN, who were receiving inpatient therapy, were exposed to 30 min of simulated PA (ie, jogging) from first-person perspective. A 360° camera had been used to professionally create a three-dimensional jogging sequence in a countryside scene. Patients wore VR goggles and followed a running track from a first-person perspective, simulating the experience of jogging themselves. Patients were able to turn their head to all sides while jogging, providing sensory information critical to creating a sense of immersion.^54^ Before and after the session, patients were asked to rate their acute urge to be physically active using a self-report questionnaire that captured cognitive, emotional and behavioural aspects.^55^ Pointing towards the utility of simulated VR movement, the single session of VR jogging led to a 14% reduction in acute activity urge scores from baseline to post session, with the within-session habituation onset (ie, reduction from peak activation) occurring after 12 min. Associations between increased autonomic nervous activity (α-amylase in saliva) and the observed reductions in the urge to move suggested a critical role of physiological activation due to the virtual jogging in explaining the effect. These findings suggest initial proof-of-concept and substantiate the main hypothesis that engaging in virtual movement decreases activity urges in patients with AN.

### Objectives

Based on recommendations for the phase-based development of novel interventions,^56^ this feasibility trial aims to obtain information required to design a full-scale, multicentric, single-blind, two-arm randomised controlled trial (RCT). The full-scale RCT will examine the effectiveness of the VR-based intervention as an add-on treatment to psychotherapy to improve activity urges and, consequently, initial treatment responses on core outcomes as targeted per AN treatment guidelines (ie, weight gain, reduction in eating disorder psychopathology). However, to advance to the full-scale RCT, it is essential to first determine feasibility. Patients may find using the VR intervention unacceptable, too difficult or cumbersome, or they may not tolerate VR-induced side effects (such as ‘cyber sickness’, see below). This could result in premature termination of trial sessions, which would threaten the hypothesised exposure effects that require minimising avoidance behaviour,^57^ and thus jeopardise completing exposure sessions. Our primary objective is to determine whether patients (1) evaluate the intervention as acceptable, (2) tolerate the interventions’ side effects and (3) will adhere to the intended intervention schedule. Our secondary objective is to estimate and assess the between-group effect of the intervention on reducing activity urges as well as the SD of the full-scale RCT’s outcome parameters, to determine the desired treatment effect and calculate the full-scale RCT’s required sample size.

### Trial design

The single-centre feasibility trial adopts the single-blind, two-arm design and outcome measures of the intended full-scale RCT in order to establish that all necessary trial components (eg, randomisation, blinding, the control intervention) work together as intended. It will evaluate feasibility as the primary endpoint and compare changes in ratings of the urge to be active between patients with AN randomly assigned to receiving VR jogging sessions and patients with AN in a control procedure (see figure 1). Progression towards the full-scale RCT will depend on meeting a set of three-tiered formal progression criteria of a ‘traffic light system’ with go (green, ie, acceptable feasibility), amend (amber, ie, potential feasibility pending trial modifications) and stop (red, ie, unacceptable feasibility) continuation signals.^58^ We will not progress to the full-scale RCT if at least one stop signal is obtained.

**Figure 1 F1:**
[figure not shown]
Trial design visual depiction. BMI, body mass index; TAU, treatment as usual; VR, virtual reality.

## Methods and analysis

### Study setting

Trial participants with AN will be recruited over the course of 16 months from one of the largest specialised eating disorder treatment facilities in Germany, located in a rural area in North Rhine-Westphalia, among inpatients receiving a multimodal disordered eating treatment based on psychodynamic and cognitive–behavioural approaches (ie, treatment as usual (TAU)). The facility’s admission statistics show that an average of 362 patients present with an eating disorder throughout a year, with 196 patients treated in 2022 meeting the key inclusion criteria for the trial (see below).

### Eligibility criteria

The trial will include patients admitted to inpatient treatment with a diagnosis of restricting or binge-eating/purging type AN according to International Classification of Diseases, Tenth Revision (ICD-10) criteria (ie, F50.00 and F50.01), with a body mass index (BMI)≤17.5 kg/m², aged 18 years or older, able and willing to provide informed consent. Only adult patients with AN will be included to reduce the influence of maturation and increase the homogeneity of treatment schedules and procedures (ie, adolescents receive family-based treatment). Patients will be recruited within the first week after admission to inpatient treatment, as we expect activity urges to be most pronounced during this phase due to the start of nutritional rehabilitation.

We will exclude patients with AN who present with severe comorbid psychiatric or somatic disorders or other conditions that may interfere with study protocol adherence and/or ability to provide informed consent (eg, severe depression, acute suicidal tendencies, relevant difficulties in spoken and written German). We explicitly refrain from excluding patients based on sex to increase sample diversity,^59^ which will benefit the generalisability of findings.^60^ However, we expect to include a significantly higher number of women due to skewed base rates in the patient population, which we will account for in statistical analyses.

### Interventions

Eligible patients will be randomised to receive the VR intervention or a VR control procedure in addition to TAU, which includes individual and group psychotherapy, psychoeducation, nutritional rehabilitation and complementary therapies (eg, art therapy). Patients will be blinded as per the different trial conditions, and we will encourage patients not to share their specific VR experiences with other therapists or patients. However, to avoid expectancy biases, all patients will be informed that the procedure aims to reduce activity urges. Both intervention and control procedures comprise 8×30 min sessions (20 min of exposure +10 min of preparation and follow-up). All sessions will be delivered by a trained doctoral researcher, with the principal investigator providing clinical supervision.

During the intervention, patients with AN will be exposed to a 20 min simulated experience of a 3D jogging sequence in a countryside scene. We chose jogging as a PA which most people may easily relate to. While standing, patients will be wearing a head-mounted display and watch a 360° video of a jogger’s running track from the first-person perspective, as if it were them actually jogging. Our previously described published pilot study showed that an average within-session habituation onset (ie, reduction from peak activation) can be expected to occur after 12 min of exposure,^28^ suggesting that 20 min sessions should produce sufficient levels of within-session effects.^57^

Following recommendations for trials with non-pharmacological interventions,^61^ we will compare the novel VR intervention to a control intervention to account for unspecific intervention components, including the amount of attention and empathy, and patient outcome expectations. Specifically, patients with AN randomly assigned to the control procedure will be exposed to a 3D, 360° stationary VR environment (similar to scenes from the jogging sequence) that have been pre-rated in terms of valence and arousal^62^ for a total duration of 20 min. They will be able to turn their head and look around but will not be exposed to any vicarious movement, and will thus be deprived of the intervention’s active component.

### Outcomes

Primary endpoints include established measures of VR intervention feasibility^63^: acceptability will be measured with the System Usability Scale (SUS)^64^; tolerability will be measured with the Simulation Sickness Questionnaire (SSQ)^64 65^; intervention adherence is measured in minutes of completed VR exposure. We will administer all assessments on a per-session basis and use the means across sessions as dependent variables. Acceptable levels of feasibility (ie, the trial progression criteria) for the primary endpoints are defined as follows: (1) normative data for the SUS suggest that average scores below 50 indicate insufficient acceptability, and scores above 70 indicate sufficient acceptability^66^; (2) empirical evidence shows that 60–95% of participants experience some level of cyber sickness during VR exposure, as determined by an SSQ Score greater than 40.^67 68^ Given its high prevalence, we deemed that cyber sickness rates (ie, proportion of patients with an average, across-session SSQ scores≥40) exceeding 95% would clearly indicate the RCT as infeasible, whereas any rates below 60% would suggest the RCT is feasible; (3) adherence, according to our pilot data, refers to completing at least 12 min of exposure, at which point habituation onset can be observed. We reasoned that adherence rates should not be lower than 50% (ie, no fewer than half of the patients should complete the minimum amount of average exposure) and that it should ideally approach the average level estimated across other VR exposure therapies (84%^69^).

Secondary endpoints include (1) outcomes relevant to the mechanism of the intervention (ie, activity urges) and (2) clinical outcomes (to be evaluated in the full-scale RCT) as targeted by AN treatment guidelines.^21^ Activity urges will be recorded on a per-session basis using the validated state activity urges questionnaire (State Urge to be Physically Active-Questionnaire (SUPA-Q)).^55^ The clinical outcomes, monitored on a weekly basis, include changes in eating disorder psychopathology using the Eating Disorder Examination-Questionnaire (EDE-Q),^70^ as well as weekly weight gain, defined by changes in patient BMI (in kg/m²), which will be obtained from patient records.

Safety and additional assessments include the rate of weight gain and potential moderators of intervention effects. Weight restoration is one of the primary goals in AN treatment.^10^ Current treatment guidelines propose weight gains of 500 g per week,^21^ though this is rarely achieved in a steady manner unless in tightly controlled settings.^24^ We reasoned the intervention would be unsafe, if successful weight gain rates in the intervention condition fall below the weight gain rates in the control condition. Potential moderators of intervention effects, to be evaluated in the full-scale RCT, include the Commitment to Exercise Scale (CES),^71^ and excessive PA status in the 28 days prior to admission, which we will assess at trial start during a face-to-face interview and categorise using the criteria: (1) ≥1 hour a day and ≥5 times a week, (2) vigorous intensity level, (3) exercise for weight or shape reasons and (4) perceived ‘obligatory’ character. Therapy motivation will be examined using the therapy motivation questionnaire (Fragebogen zur Messung der Psychotherapiemotivation (FPTM-23)).^72^ We will further conduct semistructured trial completion interviews. This includes a ‘funnelled debriefing’ procedure (ie, asking increasingly specific questions about the trial hypothesis and different treatment arms) to evaluate patient blinding,^73^ and open-ended questions concerning reasons for trial dropout or premature cessation, if applicable.

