### Participant timeline

Because changes during the first 3–4 weeks are critical for overall AN treatment outcomes,^16^,^18^ the VR intervention or control procedure will be delivered on a weekly basis over the course of the initial four consecutive weeks of AN treatment. On admission, we will screen patient records based on diagnosis, age and BMI. Patients potentially meeting inclusion criteria will be assessed for eligibility and, if eligible and willing to participate, randomised to receive the VR intervention or VR control procedure on a weekly basis over the course of the four consecutive weeks. A weekly schedule with two sessions will be implemented as we expect daily experiences (eg, supervised meals, weighing and mirror exposure as part of regular inpatient treatment) to trigger activity urges repeatedly, thus requiring regular and repeated attendance. The proposed trial duration and frequency of visits are similar to other VR-based exposure therapies for patients with AN.^49 52 74^

At enrolment, we will record patient height and body weight, and diagnosis (based on ICD-10 criteria), and patients will be asked to complete a sociodemographic questionnaire, the EDE-Q, the CES, the FPTM-23 and a brief excessive PA interview. At the end of each week during the trial, patients will complete the SUPA-Q, the EDE-Q, and we will record patients’ current weight. After each session, patients will provide acceptability and tolerability ratings, and we will record the duration of completed exposure sessions. We will record the reasons, if sessions are terminated prematurely. At close-out, we will evaluate patient blinding in a close-out interview, and record patient weight, SUPA-Q and EDE-Q scores (see figure 2).

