### Data analysis

For all primary outcomes, rate and corresponding 95% CI will be estimated with the method of Clopper-Pearson. Furthermore, for each estimated rate, it will be checked whether it is inside the red, amber or green zone. If at least one rate falls within the red zone, a decision against feasibility is made.

Repeated measures of the SUPA-Q Score will be analysed with a linear mixed effect model, using the score after the intervention as dependent variable, the score from the same day before intervention and the intervention group as fixed effect, and a random patient effect. For the other secondary outcomes, weight gain and EDE-Q, exploratory analysis will be done with a linear model (analysis of covariance (ANCOVA)), with the value at the end of treatment as dependent variable and the intervention group, the baseline value and AN subtype as independent variables.

All analyses will be done in the intention-to-treat population. For all feasibility outcomes, missing values will be imputed taking the reasons for dropout into account. We will not conduct interim analyses.

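### The only planned SUPA-Q analysis estimates an acute effect in attended sessions, not an effect of assignment in all randomised patients, yet it is to inform the size of the full-scale RCT

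*Protocol article*

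**What the plan says.** **Purpose.** The Objectives section states: "Our secondary objective is to estimate and assess the between-group effect of the intervention on reducing activity urges as well as the SD" of the RCT's outcome parameters, in order "to determine the desired treatment effect and calculate the full-scale RCT’s required sample size".

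**Timing of the SUPA-Q.** Outcomes states: "Activity urges will be recorded on a per-session basis using the validated state activity urges questionnaire". Participant timeline puts it elsewhere: "At the end of each week during the trial, patients will complete the SUPA-Q, the EDE-Q, and we will record patients’ current weight". At close-out the team will again "record patient weight, SUPA-Q and EDE-Q scores". The timeline text lists usability and tolerability ratings and exposure time after each session, but no SUPA-Q before or after a session and none at enrolment. (I could not see Figure 2, which may show more; the text sections differ all the same.)

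**Analysis.** Data analysis specifies one SUPA-Q model, a linear mixed model "using the score after the intervention as dependent variable, the score from the same day before intervention and the intervention group as fixed effect", with a random patient effect. EDE-Q and weight gain are handled differently, by ANCOVA on the end-of-treatment value adjusted for baseline. The same section adds: "All analyses will be done in the intention-to-treat population". The one imputation rule given there covers the feasibility outcomes.

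**The concern.** The SUPA-Q model can use a row only if the patient attended that day. Attendance is decided after randomisation. The group coefficient therefore describes what a session does on the day, among sessions that took place. The weekly and close-out scores, which can be taken from any inpatient whether or not VR continues, enter no analysis.

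An effectiveness trial of an add-on treatment would normally compare all patients as assigned, including those who stop. If the RCT does so, the feasibility trial followed as written will not supply a SUPA-Q effect on that basis. The team would be choosing a target effect from a different quantity under an intention-to-treat label, and could size the RCT wrongly in either direction.

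**Working it through.** **1. The plan's own figures.** The article gives no SUPA-Q effect, SD or power and no RCT sample size, so there is nothing to reproduce on this point. The per-arm sizes in Table 1 (16, 14 and 21) do reproduce with a one-sample t-test and exact binomial tests at one-sided 5% and at least 95% power. They concern the feasibility outcomes only.

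**2. Rows available to the model.** There are 8 sessions per patient and 42 patients, so at most 42 × 8 = 336 pre/post pairs. A patient who stops after session 2 gives 2 of 8 pairs. A patient who never starts gives none.

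**3. What the group term means.** For patient i at session j the model is

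post_ij = β0 + β1·pre_ij + β2·group_i + u_i + e_ij.

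β2 is the difference in post-session score between patients with the same score earlier that day. Only pre_i1 is measured before any treatment. If earlier jogging sessions lowered the starting level at sessions 2 to 8, that benefit passes through pre_ij and is not credited to β2.

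**4. Illustration.** All values here are assumptions, not figures from the documents: 200 patients per arm; 8 sessions; individual within-session effects with mean −0.40 and SD 0.30 in the jogging arm and zero in control; residual SD 0.40; average of 12 runs. Dropout, where present, leaves about 82% of sessions attended. With carry-over, 0.4 of each session's effect passes to the next starting level, and the accumulated amount halves between sessions. Simulation error of β2 is about √(0.30²/200 + 2×0.40²/(8×200))/√12 = 0.007.

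| Carry-over | Dropout | β2 from planned model | Mean within-session effect, missed sessions = 0 | Level difference carried at end |
|---|---|---|---|---|
| none | none | −0.389 | −0.389 | 0 |
| none | unrelated to response | −0.396 | −0.317 | 0 |
| none | non-responders leave | −0.419 | −0.367 | 0 |
| none | responders leave | −0.366 | −0.288 | 0 |
| 0.4 | none | −0.390 | −0.394 | −0.317 |
| 0.4 | unrelated to response | −0.397 | −0.327 | −0.220 |
| 0.4 | non-responders leave | −0.425 | −0.380 | −0.289 |
| 0.4 | responders leave | −0.369 | −0.290 | −0.182 |

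**5. Reading the table.**
- With full attendance and no carry-over the two effects agree.
- If missed sessions count as no effect, β2 is too large in every dropout row. Without carry-over the ratios are 0.396/0.317 = 1.25, 0.419/0.367 = 1.14 and 0.366/0.288 = 1.27.
- Against the −0.40 that would apply if everyone attended, β2 errs either way: −0.419 when non-responders leave, −0.366 when responders leave.
- With full attendance, β2 is −0.389 without carry-over and −0.390 with it, although in the second case a level difference of −0.317 has built up. The model does not see that difference. Measured from the score before session 1, the post-session difference late in the course would be about −0.317 − 0.390 = −0.71, so β2 understates it. A score taken away from any session would differ by about −0.32, which β2 exceeds.

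**The case against.** The strongest reply has four parts.

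- **A mixed model on all available data, by randomised arm, is not contrary to intention to treat.** This stands as far as it goes: under missing-at-random it estimates the effect if sessions are attended. That is a legitimate quantity, but not the effect of assignment.
- **The RCT may not depend on this model.** Outcomes treats activity urges as a mechanism measure and marks the clinical outcomes as those for the RCT; their SDs also feed the sizing, and their ANCOVAs do not rely on attended sessions. The RCT's SUPA-Q estimand is not stated, and if it were the same session model with similar, non-differential attendance there would be no mismatch. This stands and limits the weight of the point. It does not remove it, because the Objectives name the between-group urge effect as an input to the RCT.
- **Detail may sit in an analysis plan that is not shown.** For that reason the lack of a missing-data rule for the SUPA-Q is not counted here. The model, the label and the conflicting timing are fixed in the article itself.
- **Never-starters have no score before session 1**, so adjusting for that score would drop the very patients at issue. This is right, and the fix has to deal with it.

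A reader might go further and infer that the planned estimate overstates the RCT effect by 1/0.84 = 1.19 at the green adherence limit and by 1/0.50 = 2 at the red one. The documents do not support this. In Table 1 those percentages are shares of patients whose mean exposure is at least 12 minutes, not attendance rates: someone who attends all 8 sessions and stops each at 10 minutes is non-adherent yet can give 8 pairs. The scaling also treats an acute effect as if it were a close-out effect. Finally, the Objectives raise stopping for side effects only as a possibility, for VR in general, and both arms wear the headset for the same number of sessions. Heavier loss in the jogging arm is conjecture.

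**Conclusion.** The point holds in a limited form. Followed as written, the plan yields no SUPA-Q comparison of all patients as randomised. It yields an acute effect in attended sessions, adjusted from session 2 for a score that treatment may already have changed. Calling this intention-to-treat and carrying it into RCT planning is a mismatch.

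Neither the direction nor the size of any error is established. The estimate is too large if patients who stop gain nothing and the RCT counts them, and too small if the RCT targets benefit that accumulates across sessions. The dropout part of the gap vanishes with complete attendance. The simulated figures show the mechanism under assumed inputs and are not estimates for this trial. The matter concerns a secondary objective and leaves the feasibility decision untouched, but the correction is cheap and worth making before the effect is used for planning.

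**What to change.** 1. Make Outcomes, Participant timeline and Data analysis agree on when the SUPA-Q is taken: before and after each session, at the end of each week, at close-out, or all of these.
2. Add a between-group analysis of the weekly and close-out SUPA-Q in all randomised patients, for example a repeated-measures model, parallel to the end-of-treatment analyses of EDE-Q and weight. State that these scores are collected whether or not the patient still attends VR.
3. Adjust it for a SUPA-Q score from before the first session. Either collect that score from everyone at enrolment, or give a simple rule for a missing baseline so that patients who never start are kept.
4. Keep the session model, labelled as the acute effect in attended sessions, and report both results for RCT planning with a statement of which quantity the RCT will target.

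The cost is one extra analysis, an instruction to continue assessments that are already scheduled, one short questionnaire at enrolment if that option is chosen, and possibly a smaller reported effect.
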